# Study protocol for The GOAL Trial: comprehensive geriatric assessment for frail older people with chronic kidney disease to increase attainment of patient-identified goals—a cluster randomised controlled trial

**DOI:** 10.1186/s13063-023-07363-4

**Published:** 2023-05-30

**Keywords:** Activities of daily living, Aged, Assessment, Chronic kidney disease, Cost-effectiveness, Dialysis, Cluster randomised controlled trial, Comprehensive geriatric assessment, Frail elderly, Frailty, Functional improvement, Goal attainment scaling, Goals, Goal setting, Process analysis, Quality of life, Reablement, Recovery of function, Treatment outcome

## Abstract

**Background:**

An increasing number of older people are living with chronic kidney disease (CKD). Many have complex healthcare needs and are at risk of deteriorating health and functional status, which can adversely affect their quality of life. Comprehensive geriatric assessment (CGA) is an effective intervention to improve survival and independence of older people, but its clinical utility and cost-effectiveness in frail older people living with CKD is unknown.

**Methods:**

The GOAL Trial is a pragmatic, multi-centre, open-label, superiority, cluster randomised controlled trial developed by consumers, clinicians, and researchers. It has a two-arm design, CGA compared with standard care, with 1:1 allocation of a total of 16 clusters. Within each cluster, study participants ≥ 65 years of age (or ≥ 55 years if Aboriginal or Torres Strait Islander (First Nations Australians)) with CKD stage 3–5/5D who are frail, measured by a Frailty Index (FI) of > 0.25, are recruited. Participants in intervention clusters receive a CGA by a geriatrician to identify medical, social, and functional needs, optimise medication prescribing, and arrange multidisciplinary referral if required. Those in standard care clusters receive usual care. The primary outcome is attainment of self-identified goals assessed by standardised Goal Attainment Scaling (GAS) at 3 months. Secondary outcomes include GAS at 6 and 12 months, quality of life (EQ-5D-5L), frailty (Frailty Index – Short Form), transfer to residential aged care facilities, cost-effectiveness, and safety (cause-specific hospitalisations, mortality). A process evaluation will be conducted in parallel with the trial including whether the intervention was delivered as intended, any issue or local barriers to intervention delivery, and perceptions of the intervention by participants. The trial has 90% power to detect a clinically meaningful mean difference in GAS of 10 units.

**Discussion:**

This trial addresses patient-prioritised outcomes. It will be conducted, disseminated and implemented by clinicians and researchers in partnership with consumers. If CGA is found to have clinical and cost-effectiveness for frail older people with CKD, the intervention framework could be embedded into routine clinical practice. The implementation of the trial’s findings will be supported by presentations at conferences and forums with clinicians and consumers at specifically convened workshops, to enable rapid adoption into practice and policy for both nephrology and geriatric disciplines. It has potential to materially advance patient-centred care and improve clinical and patient-reported outcomes (including quality of life) for frail older people living with CKD.

**Trial registration:**

ClinicalTrials.gov NCT04538157. Registered on 3 September 2020.

**Supplementary Information:**

The online version contains supplementary material available at 10.1186/s13063-023-07363-4.

## Administrative information

Note: the numbers in curly brackets in this protocol refer to a Standard Protocol Items: Recommendations for Interventional Trials (SPIRIT) checklist item numbers [1, 2]. The order of the items has been modified to group similar items (see http://www.equator-network.org/reporting-guidelines/spirit-2013-statement-defining-standard-protocol-items-for-clinical-trials/).

Role of sponsor {5c}	The sponsor is the coordinating centre for the trial and is involved in overall study activities including study design, collection, management, analysis and interpretation of data, writing of the report, and decision to submit the report for publication.

## Introduction

### Background and rationale {6a}

Chronic kidney disease (CKD) is a non-communicable disease in which the structure and/or function of the kidneys have been irreversibly altered by one or more heterogeneous disease pathways, most commonly hypertension and diabetes, for a period of at least three months [3, 4]. Globally, it is recognised as a major contributor to morbidity and mortality, with an estimated population prevalence of 9.1% [5]. In Australia, CKD affects at least 1 in 10 adults (1.7 million people), is related to 16% of hospitalisations, and contributes to 10% of deaths [6, 7]. The prevalence of CKD increases exponentially with older age due to the increase in comorbid chronic diseases such as type 2 diabetes mellitus and hypertension, and an increased susceptibility to nephrotoxic agents and drugs [8]. Ninety per cent of people with moderate to severe CKD are aged 65 and above [7].

Older people with CKD have complex health needs. When compared to people seen by other specialists, those seen by kidney specialists have a higher number of comorbid conditions and medications, and more frequent institutionalisation [9]. This can make care planning challenging for older people, caregivers and the healthcare team. Managing older people with CKD will remain a pressing issue for individuals and the wider health system given the projected ageing of the population [10]. Through an enhanced understanding of this population, care planning can be more appropriate and better reflect their needs.

For those living with CKD, frailty is highly prevalent [11, 12]. Frailty is defined as a state of increased vulnerability to poor resolution of homeostasis after a stressor event, which increases the risk of adverse outcomes [13]. Frail older people are at higher risk for mortality, incident falls, hospitalisation, and worsening mobility and functional dependence [14–19]. In community-dwellers, frailty is associated with more frequent doctor visits, greater institutionalisation, social isolation, and poorer self-reported perceived health [16, 17]. Identification and quantification of frailty is important as it enables health professionals to personalise management to achieve patient-centred outcomes.

How best to manage and slow the progression of frailty is of interest to researchers and policy makers [20]. The British Geriatrics Society, Age UK, and the Royal College of General Practitioners have issued Best Practice Guidelines which recommend a comprehensive geriatric assessment (CGA) be completed for all older people identified as being frail [21]. CGA seeks to improve person-centred care by first identifying their medical, functional and psychosocial problems, and then tailoring coordinated management plans to address them [22–24]. It is of proven benefit for older people in hospital, increasing the likelihood that they will be alive and residing in their own homes at follow-up [22]. It can also prevent a decline in function and improve the quality of life for frail older community dwellers [25]. Despite CGA being featured in practice guidelines, its evidence for reducing frailty in community dwellers is of low certainty [26, 27], and the details of the essential elements of a CGA differs among clinicians [28].

To date, no research has been undertaken to specifically understand the efficacy and safety of CGA in frail older people with CKD. The GOAL trial will be the first study of the efficacy, safety and cost-effectiveness of CGA in this population, internationally. It will do so with an appreciation of the importance of person-centred care and the role patient-identified goals have in underpinning it, given attainment of their own goals is the primary outcome. The trial’s clinical relevance and utility will also be enhanced through consumer involvement, via the Consumer Advisory Board, during the trial development, conduct and dissemination of results. It features an embedded process evaluation, which will contribute to better understanding of the essential components of CGA delivered and their importance for outcome achievement.

### Objectives {7}

The primary hypothesis is that frail older people with stages 3–5/5D chronic kidney disease (CKD) who receive CGA, as opposed to usual care, have greater attainment of their self-identified goals.

The secondary hypotheses are that CGA being administered to frail older people with stages 3–5/5D CKD improves the quality of life, reduces frailty and mortality, lessens hospital admission rates and length of stay, and decreases Residential Aged Care Facility (RACF) admissions, whilst being safe and cost-effective. A process evaluation will enable the establishment of features of CGA delivery that increase the likelihood that the intervention will be effective.

### Trial design {8}

The GOAL Trial is a pragmatic, multicentre, superiority, open-label cluster randomised controlled trial. While the intervention will be implemented at the participant level, randomisation at the cluster (hospital) level has been chosen to avoid contamination of the intervention. The Australasian Kidney Trials Network (AKTN, The University of Queensland) is the sponsor and coordinating centre for the trial.

## Methods: participants, interventions, and outcomes

### Study setting {9}

Recruitment will occur at the nephrology outpatient clinics (the clusters) of 16 public hospitals across Australia, with a mix of tertiary and peripheral sites. Each hospital will form a cluster. For a cluster to be eligible for inclusion, it is expected they have a minimum of 55 older people who meet the trial’s participant eligibility criteria (noted below). The list of study sites is available elsewhere (see Supplementary file 1).

### Eligibility criteria {10}

#### Inclusion criteria

For inclusion in screening, an individual must meet both of the following criteria:Have moderate to severe CKD as determined by the treating nephrologist◦ Stage 3 = eGFR 30–59 mL/min/1.73 m.^2^◦ Stage 4 = eGFR 15–29 mL/min/1.73 m.^2^◦ Stage 5/5D = eGFR below 15 mL/min/1.73m^2^, including those receiving dialysisBe aged ≥ 65 years, or ≥ 55 if Aboriginal and/or Torres Strait Islander (First Nation’s Australians)

For those who progress to enrolment, inclusion as a study participant requires a Frailty Index (FI) of > 0.25 as measured by the FI Short Form, a validated measure in the nephrology outpatient setting [29].

An FI cut-off at 0.25 has been selected (robust [FI ≤ 0.25] or frail [FI > 0.25]) as research has demonstrated individuals who were clinically ‘apparently vulnerable’ had a mean FI of 0.22, compared to those who were ‘mildly frail’ with mean FI of 0.27 [30]. Whilst the FI is not intended to be dichotomous, for the purposes of a study design that requires a value for participant recruitment, a cut-off at 0.25 is recognised as appropriate [31]. This approach is consistent with other work undertaken within the field of frailty research [32–36].

#### Exclusion criteria

The exclusion criteria are either:Estimated life expectancy (12 months), orUnable to provide informed consent and/or participate in the Goal Attainment Scaling (GAS) process due to cognitive impairment or another reason.

### Who will take informed consent? {26a}

During clinic appointments, the sites’ principal investigators or a delegate, will approach prospective trial participants to introduce the trial, describe the study, and answer questions. Prospective participants will be provided with the Patient Information Sheet and Consent Form (see Supplementary file 2). After discussing the trial, ample time will be given to the prospective participant to enquire about the trial and decide whether to participate. If informed consent is provided, a consent form will be signed. All those who consent to participate will have the FI Short Form tool administered by a research nurse or delegate. If the FI score is > 0.25, the individual will be enrolled in the study and proceed to the completion of baseline assessments.

Since the coronavirus disease of 2019 (COVID-19) has necessitated some telephone clinic appointments rather than face-to-face appointments, the consent process may be conducted in person or remotely. Verbal consent will be available prior to conducting screening assessments and when it is permitted according to local regulations. The site investigator, research nurse or delegate will obtain informed verbal consent prior to conducting the Frailty Assessment. All staff involved in obtaining consent and enrolling participants have received specific training in the trial and the requirements of Good Clinical Practice.

### Additional consent provisions for collection and use of participant data and biological specimens {26b}

The consent process includes a provision for data linkage of research observations with state government health information systems data. No additional biological samples outside those collected as part of routine clinical care are being collected from participants. There are no ancillary studies planned.

## Intervention

### Explanation for the choice of comparators {6b}

Participating sites assigned to the control group will provide participants with usual care as per each hospital’s standard operating procedures. This group will be compared to those participants at intervention group clusters who receive CGA as an intervention in addition to usual care.

At control sites, a letter will be issued to the treating General Practitioner (GP) to inform them of a participant’s enrolment in the trial.

### Intervention description {11a}

The intervention, CGA, is a consultation completed by a geriatrician. Geriatricians are specialists who routinely undertake this task in their role of managing patients aged over 65 years. It forms a key part of their specialist training. Overviewed in Table 1 are the various components outlined in the consensus guidelines, which may be included in CGA at the geriatrician’s discretion, as determined by the participant’s individual needs [23, 37].

**Table 1 Tab1:** Domains of a comprehensive geriatric assessment—adapted from Welsh TJ, Gordon AL, Gladman JR. Comprehensive geriatric assessment—a guide for the non-specialist [23]; and, Parker SG, McCue P, Phelps K, McCleod A, Arora S, Nockels K, et al. What is Comprehensive Geriatric Assessment (CGA)? An umbrella review [37]

Domain	Components
Physical health	Comorbid conditions and disease severity Medication review Nutritional status
Psychological health	Cognition Mood and anxiety
Functioning	Mobility, balance and falls Personal and instrumental activities of daily living Transport
Social circumstances	Social networks (including family and informal support available) Accommodation
Future planning	Advance care planning Patient goals and priorities

For this trial, CGA will be delivered by the geriatrician in an outpatient clinic setting within 14 days of the baseline GAS. It is expected to take one hour (Medicare, Australia’s universal health insurance scheme, allocates 60 min for these assessments). The geriatrician will have access to the patient’s list of current medications and their medical history. When appropriate, the participant may also be accompanied by a support person (such as a spouse) who is allowed to provide collateral history to the geriatrician if warranted. This reflects routine practice.

At some hospitals, particularly teaching hospitals within the public health system, CGAs are conducted by Advanced Trainees in Geriatric Medicine with supervision from a consultant geriatrician. Advanced Trainees are doctors completing their final years of specialisation training. To increase the feasibility and generalisability of The GOAL Trial intervention, Advanced Trainees in Geriatric Medicine may complete the CGA provided they are supervised and the reports they generate are reviewed by the responsible geriatrician.

GPs often have insights into patients’ functional and cognitive problems that are not recognised or documented by hospital-based teams. The patient’s GP will be asked to consider making a referral to the geriatric outpatient clinic as per routine practice and asked to provide any additional relevant information that they feel would be relevant. This will occur once a participant is enrolled, and before they are seen in the outpatient clinic by the Geriatrician.

Following the CGA, the geriatrician will generate a letter to the treating nephrologist, GP and any other relevant specialists, which will include a comprehensive problem list and recommendations regarding an individualised care plan. The necessary referrals to allied health professionals and other specialists will be undertaken by the treating geriatrician where the site has their own Day Hospital or relevant outpatient service. Where such services are not available, the letter will request the assistance of the participant’s GP to make the required referrals to community-based providers.

The CGA intervention concludes once the geriatrician issues their letter and makes the referrals. It does not extend to ensuring a participant’s compliance with the recommendations, the GP actioning recommended medication changes, or a participant’s attendance at any referred allied health interventions.

### Criteria for discontinuing or modifying allocated interventions {11b}

The CGA will only be discontinued at the request of the participant.

### Strategies to improve adherence to interventions {11c}

Completing CGA is routine practice for geriatricians. For the purposes of this trial, and to facilitate standardisation, all geriatricians delivering the consultation will be familiarised with recent consensus guidelines which clearly define CGA [23, 37]. They will also be provided with a template which they can use for their notes if they wish. This template is provided elsewhere (see Supplementary file 3).

### Relevant concomitant care permitted or prohibited during the trial {11d}

It is expected that only a very small percentage of participants in the control group will receive CGA (2–5%) as part of their usual care. This will be recorded in the study database, to allow estimation of contamination. All other aspects of care provided will follow standard local practice for individuals with CKD being managed by a nephrologist.

### Provisions for post-trial care {30}

There are no provisions for post-trial care given the anticipated low risk of harm from a participant’s involvement in this trial.

### Outcomes {12}

Table 2 outlines the outcome measure and timepoints corresponding to each of the trial’s objectives.

**Table 2 Tab2:** Mapping of outcomes to objectives

Objective	Outcome measure	Timepoint
**Primary objective**		
To determine whether CGA in frail older people with stages 3–5/5D CKD improves attainment of patients’ own goals of care at 3 months	GAS	Baseline and 3 months
**Secondary objectives**		
To determine whether CGA improves attainments of patients’ own goals of care over time	GAS	Baseline, 3, 6 and 12 months
To determine whether CGA improves patient’s quality of life over time	EQ-5D-5L	Baseline, 3, 6 and 12 months
To determine whether CGA favourably affects the trajectory of frailty status over time	FI	Baseline, 3, 6 and 12 months
To determine whether CGA reduces mortality during the 12-month follow-up	All-cause mortality (time to event, proportion) Cause-specific mortality (time to event and proportion)	Continuous
To determine whether CGA reduces the number of hospital admissions during the 12-month follow-up	Hospital admissions (number and reason)	Continuous
To determine whether CGA reduces the hospital length of stay number during the 12-month follow-up	Hospital length of stay (days)	Continuous
To determine whether CGA reduces admissions to RACF at 12 months follow-up	Time to RACF admission	Continuous
To determine whether CGA is cost-effective within the trial context	Health care use analysis	Continuous
**Exploratory objectives**		
Patient recall of health service utilisation	Comparison of data gained from data linkage and the patient-completed Health Care Diary	Continuous
Process evaluation	Qualitative	After completion of the 12-month follow-up
**Safety objective**		
To determine whether CGA is safe when administered to frail older patients with stages 3–5/5D CKD	Any associated hospital admissions or mortality	Continuous

### Participant timeline {13}

All participants will be followed up by their respective hospitals for a total of 12 months. A SPIRIT [1, 2] diagram for the schedule of enrolment, intervention and assessments is included as Fig. 1. There will be a total of six interactions required for participants at an intervention site and five at control sites. There will be no trial-specific laboratory or radiological investigations requiring visits. Depending on the individual, a geriatrician may request further investigations as part of their CGA and referrals to other specialty services may occur. Upon completion of the trial’s 12-month follow-up, a small group of ~ 30 purposively sampled patients will be approached to participate in interviews for the qualitative data collection required for process evaluation. This interview would necessitate an additional visit.

**Fig. 1 Fig1:**
[figure not shown]
SPIRIT Figure [1, 2] showing the study schedule for enrolment, intervention and assessments

### Sample size {14}

Based on data from community-dwelling frail older adults, it is estimated that CGA will improve the GAS score by at least 10 points from an average score of 36 at baseline (which presents a change in one standard deviation, equivalent to a medium effect size) [25].

It is estimated that a cluster randomised trial with an average cluster size of 20 participants (coefficient of variation of sizes = 1) would require 16 hospital sites (clusters) with 8 sites in the intervention and control arm, respectively, to achieve 90% power to detect a mean difference in GAS score of 10 units at 3 months follow-up. This power calculation, giving a sample size of 320, assumes a common standard deviation of 10 units and an intra-cluster correlation coefficient of 0.3. To achieve sufficient power for the analysis of the secondary outcome of GAS at 12 months, an allowance for a 33% loss to follow-up over the 12 months was included, requiring baseline GAS observations from 478 participants. The 16 sites will be expected to each have a minimum of 55 patients who meet the eligibility criteria. Based on previous studies, it is estimated that approximately 10% of eligible patients will not consent to participate [26, 29] and a further 35% will not meet the frailty criteria [38] leaving a recruitment target of 500 (approximately 30 at each site). Assumptions in the sample size calculation will be re-estimated on trial data at the mid-point of the planned recruitment period.

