## Statistical methods

### Statistical methods for primary and secondary outcomes {20a}

Data will be analysed at the individual patient level. The primary outcome, Goal Attainment Scaling (GAS) scores at three months, will be analysed using a linear regression model with the intervention group as a binary covariate and baseline GAS score as a continuous covariate. To allow for the clustering of data within study centres, inference will be based on robust standard errors. Multiple imputation will be used if there is more than 5% missing data on the three-month GAS scores. Subgroup analysis of GAS scores at three months will be undertaken based on baseline characteristics of patients (including age, CKD stage, and frailty status) and study site (including unit size). Subgroup effects will be assessed via treatment-by-subgroup interactions in linear regression models.

Repeatedly measured continuous secondary outcomes (GAS scores at 6 and 12 months, EQ-5D-5L scores, FI) will be analysed using mixed models for repeated measures (MMRM) with a random intercept for the study centres and an unstructured variance–covariance matrix to model the within-patient correlation structure due to the repeated measurements. The models will have fixed effects for the intervention group, categorical time, the intervention-by-time interaction, and baseline measurements of the outcome. The primary results will be the treatment effect estimates at 6 and 12 months and 95% confidence limits.

Other secondary outcomes will be analysed using regression models appropriate for the type of outcome. The effect of CGA on the rate of hospital admission will be tested using a Poisson regression model with a random intercept for study centres and the effect of CGA on time to all-cause mortality and time to hospital admission will be assessed using Cox regression with frailty (random intercepts) for study centres. A detailed statistical analysis plan will be made public before unblinding of the trial statistician and other study personnel at the coordinating centre.

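### The stated 90% power does not belong to the stated primary analysis: at the plan's own inputs, patient-level regression with robust standard errors has about 65–71% before any gain from baseline adjustment

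*Protocol article*

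**What the plan says.** The protocol article, Sample size {14}, takes "an average cluster size of 20 participants (coefficient of variation of sizes = 1" and "assumes a common standard deviation of 10 units and an intra-cluster correlation coefficient of 0.3". From these it concludes that the trial "would require 16 hospital sites (clusters) with 8 sites in the intervention and control arm, respectively, to achieve 90% power", the target being "a mean difference in GAS score of 10 units at 3 months follow-up". The analysed total is 320, or 160 per arm. The abstract carries the figure without its conditions: "The trial has 90% power to detect a clinically meaningful mean difference in GAS of 10 units".

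Statistical methods for primary and secondary outcomes {20a} fixes the primary analysis. It is a linear regression of 3-month GAS on arm and baseline GAS, at patient level. Clustering enters only through the variance estimate: "To allow for the clustering of data within study centres, inference will be based on robust standard errors". A random intercept for centre is specified in the same section, but only for secondary outcomes.

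The sample size section credits no variance reduction from the baseline covariate. It plans to re-estimate its assumptions at the mid-point of recruitment.

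**The concern.** Robust standard errors change how the variance of the treatment effect is estimated. They do not change the estimate. With ordinary regression the arm means are patient-weighted, so a few large sites dominate when sizes vary as much as a CV of 1 implies. A mixed model with a random centre effect gives large sites less weight when the ICC is substantial, and so loses little precision from uneven sizes. The two estimators have quite different power at CV 1 and ICC 0.3, and the stated 90% looks like the second while the stated analysis is the first.

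At stake is how a null result would be read. A reader who trusts 90% takes the risk of missing a true 10-unit difference to be 10%. Under the stated analysis and inputs, with no baseline gain, it would be about 29–35%.

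**Working it through.** **Inputs from Sample size {14}.** k = 8 sites per arm, mean size m = 20, CV = 1, SD = 10, ICC = 0.3, difference = 10, n = 160 per arm.

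**Assumption.** Two-sided alpha of 0.05. The protocol gives no alpha for the power calculation or the primary test; 95% limits are mentioned only for the repeated-measures secondary models ("The primary results will be the treatment effect estimates at 6 and 12 months and 95% confidence limits").

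Throughout, SE = √(2 × SD² × DE / n), where DE is the design effect. Normal power is Φ(10/SE − 1.96). The second figure in each pair uses a t test with 14 df (16 sites minus 2).

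**Step 1. Reproduce the 90%.** For an efficiently weighted (mixed-model type) analysis:
- L = m·ICC / (m·ICC + 1 − ICC) = 6/6.7 = 0.8955
- Relative efficiency = 1 − CV²·L(1 − L) = 1 − 0.8955 × 0.1045 = 0.906
- DE = [1 + 19 × 0.3]/0.906 = 6.7/0.906 = 7.39
- SE = √(200 × 7.39/160) = 3.04
- Power = 90.8% (normal) or 86.4% (t, 14 df)

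So the 90% is reproduced with normal critical values. Ignoring size variation altogether (CV = 0, DE = 6.7, SE = 2.89) gives 93.3% or 89.4%. The latter also rounds to about 90%, but it contradicts the stated CV.

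**Step 2. The stated primary analysis.** With patients weighted equally:
- DE = 1 + [(CV² + 1)m − 1]·ICC = 1 + (2 × 20 − 1) × 0.3 = 12.7
- SE = √(200 × 12.7/160) = √15.875 = 3.98
- Power = 70.9% (normal) or 64.6% (t, 14 df)

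**Step 3. More patients per site.** At m = 30 and CV = 1: DE = 1 + 59 × 0.3 = 18.7, n = 240, SE = √(200 × 18.7/240) = 3.95, power 71.7% or 65.4%. The gain is 0.8 points. At this ICC and CV, the number and balance of sites set the precision. At m = 20, 90% would need about 14 sites per arm (normal) or 15 (t).

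**Step 4. Sensitivity to realised site sizes** (m = 20, no baseline gain):

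| CV | DE | Normal | t, 14 df |
|---|---|---|---|
| 0.4 | 7.66 | 89.8% | 85.2% |
| 0.6 | 8.86 | 85.2% | 79.8% |
| 1.0 | 12.7 | 70.9% | 64.6% |

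**Step 5. Sensitivity to the baseline covariate.** The protocol gives no correlation r between baseline and 3-month GAS. Suppose adjustment reduces within- and between-site variance equally, so that the SE is multiplied by √(1 − r²). At CV 1:

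| r | SE | Normal | t, 14 df |
|---|---|---|---|
| 0 | 3.98 | 70.9% | 64.6% |
| 0.3 | 3.80 | 74.9% | 68.7% |
| 0.5 | 3.45 | 82.6% | 76.9% |

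For 90% with normal critical values the SE must be 10/(1.96 + 1.2816) = 3.085. That requires 1 − r² = (3.085/3.984)² = 0.600, so r ≈ 0.63. With 14 df it takes about 0.70.

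**Step 6. Simulation check.** When site sizes are drawn from a gamma distribution with nominal CV 1, the CV realised over 16 sites averages about 0.92. Power averaged over those draws is about 76% (normal) or 70% (t, 14 df). With sizes fixed at a realised CV of 1.0, the empirical SE was about 3.85–3.89, or about 73–74% for a correctly sized normal test. In that fixed-size setting the robust tests behaved as follows:

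| Robust SE | Rejection at difference 10 | Type I error |
|---|---|---|
| Uncorrected, normal | 84.5% | 16.6% |
| Simple correction, t 14 df | 79.6% | 12.4% |
| Bias-reduced, t 14 df | 73.2% | 9.1% |

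None reaches 90%, and the higher rejection rates come with an inflated type I error.

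**The case against.** **The 90% is not a miscalculation.** This stands. A reader might infer an arithmetic slip, but Step 1 reproduces the figure. The fault is that it describes a different estimator from the one chosen.

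**65–71% is conditional.** This also stands. A reader might infer that the trial simply has 65–71% power. The documents do not support that. The primary model adjusts for baseline GAS, which the formula does not credit. The realised CV is not given, and a plan for about 30 recruits at every site suggests more even sizes than CV 1. At 30 per site and CV 0.4, unadjusted power would be 90.7% or 86.2%. Alpha is assumed. Still, CV 1 is the plan's own input, the 90% is stated on that input, and the sample size text takes no credit for baseline.

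**The mid-point re-estimation may deal with it.** Only in part. New values of SD, ICC or CV would not by themselves change which formula is used.

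**The primary analysis is legitimate.** A reader might infer that the regression is invalid or that a mixed model is required. Neither follows. Equal patient weighting targets the average effect over patients, and nothing here shows bias; the loss is in precision, which an interval of correct coverage would show. A small-sample correction for 16 sites may well be specified in the statistical analysis plan, which is not shown, so its absence from the article is not part of this point.

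**Conclusion.** The point holds as an inconsistency between the power statement and the primary model. At the protocol's own inputs, with two-sided alpha 0.05 and no baseline gain, the stated analysis has about 65–71% power (about 70–76% averaged over simulated site sizes with CV near 1), not 90%. Baseline correlations of 0.3 and 0.5 would raise this to about 69–75% and 77–83%; restoring 90% at CV 1 needs about 0.63–0.70. With fairly even sites (CV 0.4) the unadjusted analysis would have 85–90%. The mismatch itself is certain from the two sections. The exact shortfall is not, because it depends on the realised CV and on a baseline correlation that the protocol does not give.

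**What to change.** Make the power statement and the primary model refer to the same analysis, in the sample size section and in the abstract. Either route does this:

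1. **Keep the robust-SE regression.** Restate power as about 65–71% at CV 1 without baseline gain, state the alpha, and show the range over CV and baseline correlation as in Steps 4 and 5. This costs only a less favourable figure.
2. **Make the primary analysis a linear mixed model** with a random intercept for centre, as the secondary repeated-measures models already have, with small-sample degrees of freedom. Restate power as about 85% (86.4% with 14 df at m = 20), and keep the regression as a sensitivity analysis. This needs no more patients. However, it gives large sites less weight and so shifts the estimand if the effect varies with site size, a possibility the protocol takes seriously enough to plan a subgroup analysis by unit size. The change should be documented before unblinding.

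Under either route, the mid-point re-estimation should use the design effect of the chosen model and the observed site sizes.
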